### Data collection

Study data collectors will collect data regarding MNCH services participants received. All data will be collected using a structured questionnaire by interviewer-facilitated tablet-based face-to-face interviews or abstracted from HBRs (MCH handbook in intervention arm or prenatal card and child health card in the control arm). However, where there is no record of MNCH services received in HBRs, mother’s report of service utilisation will be used in place of the missing information as previously reported by Croft et al. [28]. Data collection will be conducted at participants’ home or at a location of her choice at two time points—at baseline and at 3 months postpartum. Table 3 shows the data collection timeline for each outcome measure.

**Table 3 Tab3:** Data collection timeline for each outcome measure

Time point	Item	Data source		Location
		Survey form	HBR	
Baseline	Participant identification	x		Healthcare facility
	Socio-demographic information	x		Participants home
	Pregnancy history	x	x	
	Household characteristics	x		
	Health behaviour	x		
	ANC utilisation	x	x	
	HBR ownership and utilisation	x	x	
Follow-up (3 months postpartum)	Participant identification	x		Participants home
	HBR ownership and utilisation	x	x	
	Health behaviour	x		
	ANC attendance and maternal health	x	x	
	Infant health and feeding practices	x		
	HBR transcripts		x	

*HBR* home-based record, *ANC* antenatal care

The baseline survey will comprise eight sections designed to elicit responses on socio-demographic factors, household characteristics, pregnancy history, maternal health behaviour and HBR ownership and utilisation. Data regarding ANC attendance, maternal health behaviour, pregnancy outcomes, infant feeding practices and infant and maternal health will also be collected from women retrospectively during the follow-up survey at 3 months postpartum. Verbal responses obtained from mothers will be double-checked against record entries made in the HBRs. In cases where discrepancies occur between the mother’s report and HBR records, the latter will be prioritised. Additionally, we will verify the quality of HBR records by referring to the facility logbook data collected from a randomly selected sub-sample of women.

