**Secondary outcomes**				
Rate of MNCH service utilisation	Total no. of actual MCH service used per person per arm compared with an expected minimum number of service utilisation. Estimate means for each arm	Continuous	No. of ANC services	No. of women with a minimum number of ANC in each arm
			Facility delivery	No of women with facility delivery in each arm
			PNC_mother	No. of women with mother PNC record in each arm
			PNC_child	No. of women with child PNC record in each arm
			Vaccination	No. of women with child vacc record in each arm
Complete CoC (service-based)	Time-dependent composite outcome. Composite outcome including ≥ 4 ANC visits + facility-based delivery + PNC of mother and newborn + complete child immunisation up to 2~3 months. Complete CoC = 1 when all indicators = 1	Binary	First ANC timing	Timeline divided into ≤ 20, 21~30, 31~37 and 38 weeks~ ga
			No. of ANC services	< 4 = 0, ≥ 4 = 1 (≤ 20 weeks); < 3 = 0, ≥ 3 = 1 (21–30 weeks); < 2 = 0, ≥ 2 = 1 (31~37 weeks); < 1 = 0, ≥ 1 = 1 (38 weeks)
			Facility delivery	No = 0; yes = 1
			PNC_mother	No HBR record = 0; HBR record = 1
			PNC_child	No HBR record = 0; HBR record = 1
			Vaccination	< 7 records = 0; 7 records = 1
Neonatal mortality	No. of deaths within the first 28 days of life compared to the total number of deliveries in each study arm. NM = 1 when all indicators = 1	Binary	Live birth	No = 0; yes = 1
			Infant death	No = 0; yes = 1
			Date of death	Death within 28 days of birth = 1
ANC service utilisation	No. of women who receive ≥ 4 ANC visits in each arm regardless of the timing of first ANC. Adequate ANC = 1 if no. of ANC services = 1	Binary	First ANC timing	1st trimester, 2nd trimester, 3rd trimester
			Received ANC	No = 0; yes = 1
			No. of ANC services	< 4 = 0; ≥ 4 = 1
	No. of women who receive ≥ 8 ANC visits in each arm regardless of the timing of first ANC. Adequate ANC = 1 if no. of ANC services = 1	Binary	First ANC timing	1st trimester, 2nd trimester, 3rd trimester
			Received ANC	No = 0; yes = 1
			No. of ANC services	< 8 = 0; ≥ 8 = 1
Facility-based delivery	No. of facility-based deliveries in each arm.	Binary	Facility delivery	No = 0; yes = 1
Infant health check-up	Presence of at least one HBR entry from baby-well clinic attendance.	Binary	Record entry for any of current wgt, polio1, pentavalent, pneumo1 or rota1	No HBR record = 0; HBR record (for any of current wgt, polio1, pentavalent, pneumo1 or rota1) = 1

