### Other secondary outcomes

Rate of MNCH service utilisation—number of actual MNCH service usedNeonatal mortality—number of infant deaths within the first 28 days of lifeANC service utilisation—frequency of ANC service use in each armFacility-based delivery—number of facility-based deliveries in each armInfant health check-up—proportion of children who received infant health checksMaternal morbidity and pregnancy complication detection rate—number of cases of specified disease conditions and pregnancy complications diagnosed by a health care providerInfant morbidity rate—number of specific childhood disease cases attended by a health care providerInfant mortality—number of infant deaths in each study armMaternal health behaviour—prevalence of maternal health behaviour between arms measured using at baseline and follow-upMaternal depression—number of cases of maternal postnatal depressive symptomsInfant feeding practices—prevalence of appropriate infant feeding practices in each study armChild vaccination—number of fully vaccinated children at the end of the study period

All outcomes will be assessed at follow-up except otherwise stated, and data will be collected through structured interviews and abstracted from HBRs.

The minimum number of MNCH services required for maternal behaviour-based CoC completion is shown in Table 5 and will depend on the timing of the first ANC visit and exposure to the intervention.

**Table 5 Tab5:** Minimum expected number of service utilisation to achieve complete CoC (primary outcome)

Time of first ANC (weeks)	ANC	Del	PNCm	PNCc	Vacc	Total	Complete CoC
≤ 20	4	1	1	1	2	9	4 ANC, del., PNCm, PNCc, 2 vacc visits
21~30	3	1	1	1	2	8	3 ANC, del., PNCm, PNCc, 2 vacc visits
31~37	2	1	1	1	2	7	2 ANC, del., PNCm, PNCc, 2 vacc visits
38~	1	1	1	1	2	6	1 ANC, del., PNCm, PNCc, 2 vacc visits

*ANC* antenatal care, *del.* facility delivery, *PNCm* postnatal care for mother, *PNCc* postnatal care for child, *vacc* two vaccination clinic visits at birth and 2 months infant age

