### Statistical analysis

The intervention arm (MCH handbook) will be compared to the control (traditional use of two stand-alone HBRs) in the main analysis. We will conduct descriptive analysis, and baseline data from the intervention and control arms will be analysed for comparability of baseline characteristics. Rates of missing data for each variable will be determined to assess the differences between the arms, and overall losses to follow-up will be determined. We will report reasons for losses within each arm and compare the reasons qualitatively.

We plan to measure intervention impact using two analysis sets: the intention-to-treat (ITT) set and the per-protocol analysis set (PPS). The ITT population will include all participants within the randomised municipalities analysed according to the municipality where they were first registered to receive MNCH services (i.e. discounting where they received second, third or fourth MNCH services) [33, 34]. The ITT population will be the primary analysis set, and all analyses will be conducted using this population unless otherwise stated. In the PPS, participant data will be analysed according to the treatment they actually received. Data from the participant with more than one MCNH service utilisation in the control arm will be included in the control arm regardless of the municipality of first registration for MNCH services in the PPS analysis.

The primary endpoint in this impact evaluation study is to compare the proportion of CoC completion achieved among mothers who received the MCH handbook in the intervention arm and those who received the traditional stand-alone HBRs in the control arm. We will evaluate the effect of the provision of MCH handbooks on CoC completion at the municipality level using a generalised linear mixed model (GLMM) assuming logit link and binomial distribution. All analyses will be based on complete case analysis. Regarding the number of healthcare service utilisations, the analysis will be conducted using survival analysis. We will also evaluate the intervention effects in a subgroup of participants based on socio-economic status, urban/rural residence and other baseline characteristics while accounting for cluster effect.

All analyses will be done using STATA (version 13 or higher, Stata Press, College Station, TX).

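### Survival analysis is assigned to the number of services used, although Table 4 defines that outcome as a per-woman count with means by arm

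*Protocol article*

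**What the plan says.** The protocol article describes this outcome in several places.

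- **Method (Statistical analysis).** "Regarding the number of healthcare service utilisations, the analysis will be conducted using survival analysis". No event, time origin, time scale, censoring rule or recurrent-event model is given.
- **Outcome (Table 4, rate of MNCH service utilisation).** "Total no. of actual MCH service used per person per arm compared with an expected minimum number of service utilisation". The type is continuous and the summary is "Estimate means for each arm". The list under Other secondary outcomes also describes it as a number of services.
- **Indicators (same row of Table 4).** There are five, and each is a number of women. The first is "No. of women with a minimum number of ANC in each arm".
- **Expected minimum (Table 5).** 9, 8, 7 or 6 services for a first antenatal visit at up to 20, 21 to 30, 31 to 37, or 38 weeks and later.
- **Timing of assessment (Data collection).** Data are collected "at two time points—at baseline and at 3 months postpartum". Outcomes are assessed at the later survey unless otherwise stated.
- **Incomplete data (Statistical analysis).** "All analyses will be based on complete case analysis".

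**The concern.** The article names an outcome, a summary measure and a method, and the method does not match the other two. Table 4 promises a contrast in how much care women used. Survival analysis in its ordinary form compares how soon an event happens among those still at risk of it. That is a different question, and no event is defined.

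This is the first secondary outcome listed in Table 4, and it measures the trial's stated aim most directly. If the sentence is followed, the reported effect would be a hazard ratio or similar. A reader could not translate that into more or fewer services per woman, and it need not agree with the means shown beside it.

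**Working it through.** The protocol gives no figure for this point to reproduce, so the check compares its statements, with some arithmetic.

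**1. Expected minimum.** From Table 5, antenatal visits + delivery + postnatal care for mother + postnatal care for child + vaccination visits:

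- up to 20 weeks: 4 + 1 + 1 + 1 + 2 = 9
- 21 to 30 weeks: 3 + 1 + 1 + 1 + 2 = 8
- 31 to 37 weeks: 2 + 1 + 1 + 1 + 2 = 7
- 38 weeks and later: 1 + 1 + 1 + 1 + 2 = 6

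The totals agree with the table. Table 5 is labelled for the primary outcome. I assume that it also supplies the expected minimum named in Table 4, since no other is given.

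**2. Is any outcome a time to event?** None in Table 4 is. The two continuum-of-care outcomes called time-dependent are binary, and they use the timing of the first antenatal visit only to set the number of visits required. Neonatal mortality uses a date of death only to form a yes/no variable.

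**3. What each statement estimates.** Let N be the services a woman used and E her expected minimum. Table 4 asks for the arm mean of N relative to E. For a count, mean N = sum over k ≥ 1 of P(N ≥ k), which does not depend on when the services occurred. A hazard comparison, for example of time to the k-th service, depends both on P(N ≥ k) and on when that service occurs.

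**4. Is there a role for censoring?** The survey ends the observation at the same point after birth for every woman who completes it, and women without complete data are left out. The usual reason for survival methods, partial follow-up, is therefore absent as written. Women do enter at different gestational ages, but Table 5 already allows for this through the smaller minimum.

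**5. Do the indicators produce the count?** If each of the five is read as yes/no for one woman, their sum is at most 1 + 1 + 1 + 1 + 1 = 5. That is below the smallest Table 5 total, 6. The indicators therefore cannot yield the per-woman number that the definition describes.

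**6. Illustration with assumed inputs, none from the protocol.** The set-up was 5,000 women per arm without clustering, Poisson counts with mean 6 or 6.6, visit times drawn as 40 × Beta(a, 2) weeks, and a Cox model for time to the fourth service with censoring at 40 weeks. The average visit time is 40a/(a + 2): 15 weeks for a = 1.2, 20 for a = 2 and 24 for a = 3. Hazard ratios are for the second arm against the first.

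| Mean count, first v second arm | Average visit week, first v second arm | Hazard ratio |
|---|---|---|
| 5.99 v 5.98 | 20 v 20 | 1.02 |
| 6.05 v 5.98 | 20 v 15 | 1.36 |
| 5.98 v 6.60 | 20 v 20 | 1.23 |
| 5.99 v 6.60 | 20 v 24 | 0.86 |

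A hazard ratio can move away from 1 when mean use is practically equal, and can fall below 1 when mean use is higher. This shows only that the two measures can separate. It does not predict what this trial would show.

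**The case against.** The best defence is that survival methods can be made to fit a count. The number of services can itself serve as the time axis: a woman starts at 0, the event is dropping out of the care pathway, and she is censored on reaching her required total K. Without censoring, the area under that curve is the mean count, by the identity in step 3 of the working. A mean cumulative function for dated, recurrent services also estimates a mean. Some timing data exist, since antenatal use is recorded at baseline as well as at follow-up and the week of the first visit is an indicator. On this view the article has only left out a specification, and the means in Table 4 are a descriptive summary beside the model.

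Part of this stands. It would be wrong to say that no survival method could ever estimate mean use, or that the count is reconstructed from the last survey alone. But the article describes none of these approaches. Under the pathway reading with censoring at K, the area up to K is the mean of min(N, K), a capped count and not the services actually used. An ordinary hazard ratio from any of them is still not a contrast in means. Further detail elsewhere could add an event and an origin, but one of the two published statements would still have to change.

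Stronger readings are tempting but are not supported:

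- **Survival analysis would favour late entry.** With 40 weeks' gestation, entry at week 35 leaves 5 weeks to delivery and entry at week 15 leaves 25, a ratio of 25/5 = 5. This assumes enrolment as origin and delivery as event, and the article states neither. It also compares two women, not two arms.
- **The count is bounded at 6 to 9.** Table 5 gives minima. Actual use can exceed them, and eight or more antenatal visits is a separate secondary outcome.
- **The result would point the wrong way.** The illustration shows that this can happen under chosen inputs, no more.

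**Conclusion.** The point holds as a mismatch between two things the article itself states: a continuous per-woman count summarised by means, and a survival method for that same number. A hazard-based comparison would not estimate the stated contrast. The two could differ if the timing of entry or of visits differs between arms. The protocol gives no data on such differences and no event or origin, so neither size nor direction can be derived.

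The conclusion rests on reading survival analysis in its usual hazard-based sense, and on taking the healthcare service utilisations of the analysis sentence to be the Table 4 outcome of that kind. No other outcome in the table fits as closely.

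The point is limited to one secondary outcome. A reader might infer that the trial's main result is at risk. It is not: the primary binary outcome has its own logistic mixed model. The text should be corrected before analysis.

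**What to change.** Replace the survival sentence with a model for the uncapped number of services per woman. Either of these would do:

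- a Poisson or negative binomial mixed model with the log of the Table 5 expected minimum as offset, reporting a rate ratio; or
- a linear mixed model for the ratio of actual to expected services, reporting a mean difference.

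Both should include a random effect for municipality and be shown with the arm means that Table 4 already promises. The count should not be capped at the expected minimum, because that would discard use above it and change the outcome.

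In the same edit, state that Table 5 supplies the expected minimum for this outcome. Reword its Table 4 indicators so that they give services per woman instead of numbers of women per arm.

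The cost is one replaced sentence and a small change to one table row. The planned surveys and record abstraction already cover these services, so no extra data collection is needed.

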### Losses to follow-up

Participants who do not provide any baseline or follow-up data and those who withdraw their consent to participate in the study will be regarded as being lost to follow-up. To minimise such losses, a participant identification form will be used to collect each woman’s contact information in as much detail as possible, including GPS location where baseline interview was conducted to facilitate repeat contact with mothers during the follow-up survey. The proportion of participants lost to follow-up will be compared between the two arms.

### Data management and storage

All data collection processes will be standardised across the 10 municipalities. At each healthcare facility, pregnant women seeking MNCH services and eligible to join the study will be listed in the study register maintained by a data collector. Following enrolment, each woman will be given a unique identification number. A standardised tablet-based data collection form will be administered to each woman by trained study data collectors at baseline and follow-up. To ensure completeness of each record, virtually, all questions in the form are required, while at the same time ensuring participants right to voluntary participation. Completed forms will be uploaded to a secure server at the end of each day. The datasets will be password-protected and only accessible to the data manager.

We will not establish a third-party data monitoring committee due to the nature of the intervention and study design. However, periodic meetings involving all members of the study team will be held weekly to review the processes and progress related to the following: (1) participant recruitment and interviews; (2) completeness, accuracy and timeliness of uploading completed survey forms to secure server; and (3) any other logistical issues related to the study.

### Risk and benefit

The intervention in this study is non-invasive and carries a less than minimal risk for adverse events in participating women. Consequently, potentially serious outcomes are not anticipated, and we do not envisage any reason, due to the intervention or study design to end the trial prematurely. Therefore, we will not conduct an interim analysis. Notwithstanding, disclosure of personal information and time taken for survey interviews may cause some discomfort to some participants. Data collectors will assure each participant of the anonymity and confidentiality of the data collected to make participants at ease. Adverse events that may arise will be assessed by the study team and reported to the responsible ethics committee. Reporting will include the type of event, circumstances, the extent of connection with study activities and the response provided. Potential benefits to participants in the study include improved CoC completion, knowledge of recommended health practices during pregnancy, recognition of danger signs and care of mother and newborn. Moreover, the intervention package will be delivered through the existing healthcare system for obtaining MNCH services.

## Discussion

This is a study protocol for a cRCT aimed at estimating the impact of an intervention package—including the distribution of MCH handbook and its supplementary interventions to pregnant women, compared with the traditional use of two stand-alone HBRs on the utilisation of services provided at healthcare facilities from pregnancy through the postnatal and early childhood period. Few studies have shown that proper utilisation of HBRs could promote continuity of maternal and child health care [14, 16, 35], and WHO recommends that each pregnant woman carries her own HBRs during pregnancy to improve continuity and quality of care [36]. Notwithstanding, the superiority of the integrated MCH handbook over other alternatives is an area of research in which there is a dearth of gold standard trials [15, 37]. We will attempt through this trial to provide higher quality evidence to demonstrate the benefits of implementing the MCH handbook over traditional stand-alone HBRs.

As a cluster-level intervention package, the trial employs a population-based approach to ensure uniform distribution of the MCH handbooks and its supplementary interventions. A cRCT is the preferred design in this trial to minimise logistical and scientific difficulties such as contamination between clusters and to optimise conditions to bring the intervention to scale within Angola in a real-life context. The trial’s efficiencies lie in its design and data collection methods. The intervention package will be administered through the existing healthcare system for delivering MNCH services and with the support from the regional and local health divisions who routinely supervise the activities of frontline healthcare providers. Data will be collected through tablet-based interview methods. Mobile tablet devices have become an important tool for collecting primary data in clinical research, using a combination of functions including data entry, audio recorders, cameras, barcode readers and global positioning system receivers [38]. Using this method, the data management team in this trial will more easily collect and link data from the baseline and follow-up surveys. Mobile phones have also become an important tool for follow-up in public health research, through calls and text messaging [39, 40]. In order to reduce attrition rates, we will ask each participant to complete a participant identification form providing information to facilitate repeat contact [39, 41].

The findings from the impact evaluation study will be shared with the Angolan government and are expected to form a basis for revising the current trial version of the MCH handbook and for making an informed policy decision on nationwide scale-up and distribution of the MCH handbook. We plan to disseminate study findings through conference presentations and publication in international peer-reviewed journals.

This study protocol has been reported in accordance with the SPIRIT guidelines (Additional file 1) and including all items from the World Health Organization Trial Registration Data Set (Additional file 2).

